### Concealment mechanism {16b}

To guarantee the concealment of the randomization sequence, the randomization codes will be kept in opaque envelopes with correlative numerical identification that will be opened once it has been verified that the patient meets the inclusion criteria and has signed the informed consent form.

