#### Abdominal-wall closure technique — intervention group

In the intervention group, once the closure in 2 muscle-aponeurotic planes with continuous synthetic suture described in the previous paragraph has been completed, the closure will be completed by placing the ProGrip® macroporous polypropylene monofilament mesh in supra-aponeurotic position using the surface with PLA microgrips, which act as Velcro, in direct contact with the superficial aponeurotic plane constituted by the aponeuroses of the greater oblique muscle and the crescentic line of the anterior rectus abdominis muscle. The PLA microgrips provide immediate fixation, making additional fixation with stitches unnecessary, which makes the technique very easy to use and systematize among the different surgeons of the transplant team. The procedure is completed with the placement of a low-calibre round Jackson-Pratt subcutaneous drain (10F) connected to a vacuum system.

The mesh implant technique is based on a PRIMA multicentre, double-blind, randomized controlled trial which shows that only reinforcement mesh decreases incisional hernia without increasing complication rates with respect to primary closure [16].

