### Criteria for discontinuing or modifying allocated interventions {11b}

The patient will be able to revoke his/her consent at any time until surgery. The kidney transplant surgeon will be able to modify intervention allocation if the local or patient general condition does not advise to carry out the assigned abdominal-wall closure technique. No other modification of allocated intervention will be possible once abdominal-wall closure is completed.

This modification must be adequately justified and will be taken into account during data analysis (intention-to-treat and per-protocol analysis).

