### Participant timeline {13}

Informed consent for the study will be obtained prospectively at the time of the visit corresponding to the pre-transplant evaluation. For patients previously included in the renal transplant waiting list, informed consent will be obtained at the time the patient is called as a potential renal transplant recipient. In either case, once the corresponding consent has been obtained, the patient's clinical history and physical examination will be reviewed and the inclusion–exclusion criteria will be revised. Assignment to treatment will be randomized. The concealment of the randomization sequence will be performed by means of opaque numbered envelopes that will be opened after verifying that the patient meets the inclusion criteria of the study. Assignment to the treatment group will be communicated to the surgeon responsible for the transplant. Follow-up visits will be performed at 3, 6, 12 and 24 months post-transplantation.

The follow-up duration is based on a cohort from our centre consisting of 130 transplant patients during the years 2016 and 2017. This cohort was analysed together with the General and Visceral Surgery team, and we found that 25% of the transplant patients had experienced an incisional hernia within the following 2 years after transplantation. The median time for the development of the incisional hernia was 17.1 months (IQR: 2.6–23 months). Furthermore, the literature supports these timeframes, as most incisional hernias occur within the first 2 years following surgery, particularly when the surgery is elective [16–18].

The following figure shows the template of content for the schedule of enrollment, interventions and assessments (Standard Protocol Items: Recommendations for Interventional Trials (SPIRIT) Figure) (Fig. 1).

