### Implementation {16c}

Allocation sequence will be generated by the hospital’s Clinical Biostatistics Unit. Participants will be enrolled by the principal investigator ([name]) and all the members of the transplant surgery team ([name], [name], [name], [name], [name]). Each transplant surgery team member will review patient’s informed consent, clinical history and physical examination and inclusion–exclusion criteria will be revised on the day of transplantation. An opaque numbered envelope stratified by BMI prepared by the hospital’s Clinical Biostatistics Unit will be opened by a member of the surgical transplant team on call and the treatment group communicated to the surgeon responsible for the transplant.

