## Statistical methods

### Statistical methods for primary and secondary outcomes {20a}

The primary analysis will be by intention-to-treat (ITT), including all randomized patients who have undergone renal transplantation. A per-protocol analysis will also be performed with all patients. Demographic and clinical parameters will be described by mean and standard deviation or median and its confidence interval for continuous variables depending on the normal or non-normal distribution of the sample. Categorical variables will be described by absolute and relative frequencies. In addition, differences between groups will be calculated using Student’s *t*-test or Mann–Whitney *U* test depending on the sample distribution and the chi-square test. Time to incisional hernia onset will be described by Kaplan–Meier survival analysis and compared by log-rank test. The analysis will include stratification by the variable “obesity”. A *p*-value < 0.05 will be considered statistically significant. We performed our analyses with Stata v16.1 (StataCorp, TX, USA).

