Regarding factors specifically related to the surgical wound, the type of incision and surgical wound infection have been identified as risk factors [13, 19]. Different approaches to renal transplantation have been described including paramedial, oblique, extended groin, pararectal and field hockey stick incisions [1, 2, 4, 19]. Systematic reviews in the context of general surgery have shown that paramedian and transverse incisions have a lower incidence of incisional hernia [10, 11, 15, 20, 21]. The 2 most commonly used approaches are the oblique hockey stick approach from 2 cm above the anterior superior iliac spine to the pubis, involving the greater and lesser oblique and transverse muscles, and the external pararectal incision from 3 cm above the umbilicus to the pubis, involving the aponeurosis instead of the muscle. Paramedian incisions are similar to field hockey sticks and pararectal incisions in that they all use the lunate ligament at the lateral border of the rectus abdominis muscle to gain access to the retroperitoneal space in the iliac fossa. In contrast, oblique and extended inguinal incisions are also similar and extend laterally parallel to the muscle fibres of the external oblique. Studies comparing the incidence of incisional hernia between the field hockey stick incision and oblique incisions show, in principle, a lower incidence in the latter [2, 4, 19]. In fact, European surgical guidelines recommend transverse incisions not only because of a reduced incidence of incisional hernia but also because of a lower analgesic requirement [10, 15, 20]. Nanni et al. compared both types of incisions showing a reduction in the incidence of incisional hernia by abandoning the hockey stick incision and the extensive muscle section [19].

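### The envelope can be opened before surgery although the arms differ only after a shared closure, so the surgeon may close and decide on overrides knowing the arm; the per-protocol set is also misdefined

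*Protocol article*

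**What the plan says.** **When the arm is revealed.** Section {16b} has the envelope "opened once it has been verified that the patient meets the inclusion criteria and has signed the informed consent form". Section {13} says the same of "opaque numbered envelopes that will be opened after verifying that the patient meets the inclusion criteria of the study". Section {16c} adds that "inclusion–exclusion criteria will be revised on the day of transplantation" and that the envelope is "opened by a member of the surgical transplant team on call and the treatment group communicated to the surgeon responsible" for the transplant. No section makes opening wait for any step of the operation.

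**Where the arms diverge.** In the intervention group the mesh is added "once the closure in 2 muscle-aponeurotic planes with continuous synthetic suture described in the previous paragraph has been completed". The control group has a two-plane continuous sutured closure by the small-bites technique and, for masking, the same subcutaneous drain. The article's order obscures the cross-reference in the intervention section, because the two-plane closure is described in the control section that follows it. I read the two closures as the same.

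**Who is blinded.** Section {17a} lists participants, outcome assessors and the data analyst. The surgeon is not listed.

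**Overrides and analysis sets.** Section {11b} states: "The kidney transplant surgeon will be able to modify intervention allocation if the local or patient general condition does not advise" the assigned closure. Such changes must be justified and are to be reflected in the intention-to-treat and per-protocol analyses. Section {20a} defines the primary ITT set as "including all randomized patients who have undergone renal transplantation. A per-protocol analysis will also be performed with all patients".

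**The concern.** Nothing before the end of the fascial closure requires anyone in theatre to know the arm. If the surgeon knows it, the shared closure is done with or without the knowledge that a mesh will reinforce it. The Discussion counts closure technique among the incision-specific factors to which hernia appears to be related, and it describes the small-bites method in terms of bite size, stitch spacing and suture-to-wound ratio, all of which depend on the operator. A difference in care between arms at this step would act directly on the primary outcome. Blinding the patient, assessor and analyst would not remove it.

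The override raises a similar problem. A judgement about local condition, much of which can only be seen during surgery, may be made by someone who already knows which closure was assigned. A written justification documents that decision but does not make it independent of the arm.

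The analysis meant to handle overrides is also misdefined. A per-protocol analysis that includes everyone does not set apart patients who did not receive their allocated closure, which is what {11b} needs it to do.

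**Working it through.** **1. Timing, from the text.**
- {13} and {16b}: the trigger is verified eligibility and signed consent.
- {16c}: that review takes place on the day of transplantation, and the arm then goes to the surgeon.
- {20a}: ITT is limited to randomised patients who were transplanted. That limit has a purpose only if a patient can be randomised and then not transplanted.

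Together these imply that the arm is usually known before the operation. They do not state it, and they do not place the opening relative to incision.

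**2. Divergence, from the text.** Both arms: two-plane sutured closure and subcutaneous drain. Intervention only: mesh laid on after that closure. The arm is first needed when the two planes are closed.

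**3. The plan's sample size.** Inputs from {14}: p1 = 0.20, p2 = 0.05, alpha 0.05, power 80%, 76 per group. Sidedness is not stated; two-sided reproduces the figure. With pooled variance and no continuity correction,

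n = [1.960·√(2p̄(1−p̄)) + 0.842·√(p1(1−p1) + p2(1−p2))]² / (p1−p2)²

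- p̄ = 0.125, so √(2 × 0.125 × 0.875) = 0.4677
- √(0.16 + 0.0475) = 0.4555
- n = (0.9167 + 0.3834)² / 0.0225 = 75.1, rounded up to **76**, which matches

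Power at n = 76 is Φ{[(p1−p2)√n − 1.960·√(2p̄(1−p̄))] / √(p1(1−p1) + p2(1−p2))} = Φ[(1.3077 − 0.9167) / 0.4555] = Φ(0.858) = **80.5%**.

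**4. Illustration of override dilution.** The protocol gives no override rate, so a share c is assumed. If c of the mesh arm receives no mesh, has the control rate and is analysed as randomised, the mesh-arm rate is 0.05 + 0.15c. If the same share of controls also receives mesh, the control rate is 0.20 − 0.15c.

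| c (assumed) | Mesh-arm rate | Power, mesh-to-no-mesh only | Power, both directions |
|---|---|---|---|
| 0 | 5.00% | 80.5% | 80.5% |
| 5% | 5.75% | 75.1% | 71.5% |
| 10% | 6.50% | 69.3% | 61.1% |

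To restore 80% power in the one-direction case would take 86 per group at 5% and 98 at 10%.

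**5. Untransplanted patients.** If 76 per group counts randomised patients and 2%, 5% or 10% (assumed) are not transplanted, 74, 72 or 68 remain per group and power is 79.4%, 78.3% or 75.9%.

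**6. What cannot be calculated.** The documents give nothing from which to estimate how far knowledge of the arm would change the closure. Steps 4 and 5 do not measure that.

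**The case against.** The strongest reply is that this is an acceptable design choice: the surgeon is never claimed to be blinded, the team has been specifically trained and has unified its technique with only minor variation, and the control closure is specified down to the suture. That stands as mitigation. It narrows the room for performance bias without removing it, and knowledge of the arm during the common closure serves no purpose.

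Several stronger readings are tempting, but the documents do not support them.

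- **Concealment is broken.** It is not. Eligibility and consent come before opening.
- **The arm is stated to be known before incision.** It is not stated. This is an inference from the trigger and the ITT wording.
- **Knowledge of the arm would steer a prognostic choice of incision.** The Discussion does say that "the type of incision and surgical wound infection have been identified as risk factors". But it and the surgical technique section treat the three permitted incisions as sharing the same route, and the transplant comparison cited is with oblique incisions, which the trial does not list. No hernia gradient across the three is shown.
- **Early opening creates overrides.** Under {11b} they arise from the patient's local or general condition, whenever the envelope is opened. Timing affects only whether the decision is made with the arm known. ITT keeps these patients in their randomised arm, so the harm there is mainly dilution.
- **Leaving out untransplanted patients biases the result.** It does so only if non-transplantation depends on the arm, which nothing suggests, and such patients have no transplant incision in which to develop a hernia. The set is a modified ITT under an ITT label.
- **The power loss measures the main problem.** It does not. It rests on assumed override rates.

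One may also say that the per-protocol wording is a separate matter, and that {11b} promises overrides will be taken into account. It is separable from envelope timing, but as written the set does not deliver what {11b} promises.

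**Conclusion.** The point holds as an avoidable risk of performance bias at the step just before the randomised one, and as an override decision that may be made with the arm known. It rests on two readings: that the envelope is usually opened before the operation, which is implied but not stated, and that both arms receive the same sutured closure. The size and direction of any bias are unknown.

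The per-protocol definition in {20a} is wrong as worded, because a set of all patients cannot separate those who did not receive the allocated closure.

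The fall in power from 80% to 75% or 69% assumes 5% or 10% of the mesh arm overridden to no mesh, with a 20% hernia rate in those patients. It shows why overrides should be few and reported. The sample size of 76 per group is itself correct for its stated inputs. The change is worth making because it is cheap.

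**What to change.** - **{13}, {16b}, {16c}:** keep the checks of eligibility and consent, but open the envelope in theatre only after the two-plane closure is complete and the surgeon has recorded that either allocation is acceptable. Which conditions make an allocation unacceptable remains a clinical matter for {11b} and is not judged here.
- **{20a}, ITT:** all randomised patients. With the later opening every randomised patient has been transplanted, so the restriction is no longer needed. If the timing is not changed, call the set a modified ITT and report by arm how many were randomised but not transplanted.
- **{20a}, per-protocol:** patients who received the allocated closure, in place of all patients.
- **Reporting:** any remaining overrides, with reasons, by arm; and the number who consented but were not randomised. Section {26a} already treats signed consent as enrolment, so enrolment and randomisation can be counted separately.

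The cost is amendment wording and a small change in theatre routine, since a member of the on-call team already opens the envelope. There are two downsides. A mesh must be on hand for every case. Some patients who would have been overridden become exclusions before randomisation, which slightly narrows the population to those in whom either closure is acceptable.

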### Implementation {16c}

Allocation sequence will be generated by the hospital’s Clinical Biostatistics Unit. Participants will be enrolled by the principal investigator ([name]) and all the members of the transplant surgery team ([name], [name], [name], [name], [name]). Each transplant surgery team member will review patient’s informed consent, clinical history and physical examination and inclusion–exclusion criteria will be revised on the day of transplantation. An opaque numbered envelope stratified by BMI prepared by the hospital’s Clinical Biostatistics Unit will be opened by a member of the surgical transplant team on call and the treatment group communicated to the surgeon responsible for the transplant.

## Assignment of interventions: blinding

### Who will be blinded {17a}

#### Trial participants

In order to achieve masking of the participating subject, a small-bore (10F) Jackson-Pratt drain connected to a vacuum system will be placed in the subcutaneous space at the end of the procedure in a manner similar to the intervention group. In both treatment groups, the subcutaneous drain will be removed on post-transplant day 2 or 3. Placement of this drain is not associated with increased patient risk.

#### Outcome assessors

The outcome assessor will belong to the General and Visceral Surgery team that is not directly involved with the transplantation procedure and agrees not to verify the assignment in the transplantation surgical protocol.

#### Data analyst

Masking of the analyst is achieved through collaboration with the Clinical Biostatistics Unit in the data analysis of the study (independent analyst) using a pseudo-anonymized database.

### Procedure for unblinding if needed {17b}

Unblinding will be permissible if severe surgical site complication (infection, pain) develops that requires mesh retirement. Only the principal investigator will be authorized to reveal a participant’s allocated intervention during the trial.

## Data collection and management

### Plans for assessment and collection of outcomes {18a}

All information collected during the conduct of the study will be recorded directly in the data collection notebook under the REDCap data capture software distributed through the REDCap consortium that provides computer support for clinical investigators and managed by the Central Bioinformatics Support Unit of the Hospital’s Health Institute (IRYCIS) and will be kept in the strictest confidentiality, to which only the investigators participating in the study, the institutional review board (IRB) and the competent authorities will have access. When a correction is made, the date and the initials of the person making the correction should be noted and his or her signature added.

### Plans to promote participant retention and complete follow-up {18b}

Not applicable. Kidney transplant patients’ adherence to follow-up is usually high.

### Data management {19}

Data will be included in a database that follows the current regulations on Personal Data Protection (Regulation (EU) 2016/679 of the European Parliament and of the Council of 27 April 2016 on Data Protection (RGPD) and the Organic Law 3/2018, of 5 December, on Personal Data Protection and guarantee of digital rights). All information collected during the conduct of the study will be recorded directly in the data collection notebook under the REDCap data capture software distributed through the REDCap consortium that provides computer support for clinical investigators and managed by the Central Bioinformatics Support Unit of the Hospital’s Health Institute (IRYCIS) and will be kept in the strictest confidentiality. The study subjects will be only identified with a numerical code.

### Confidentiality {27}

Data will be included in a database that follows the current regulations on Personal Data Protection (Regulation (EU) 2016/679 of the European Parliament and of the Council of 27 April 2016 on Data Protection (RGPD) and the Organic Law 3/2018, of 5 December, on Personal Data Protection and guarantee of digital rights). All information collected during the conduct of the study will be recorded directly in the data collection notebook under the REDCap data capture software distributed through the REDCap consortium that provides computer support for clinical investigators and managed by the Central Bioinformatics Support Unit of the Hospital’s Health Institute (IRYCIS) and will be kept in the strictest confidentiality.

The information disseminated and obtained by the implementation of this study is considered confidential and should be treated as such at all times. The study subjects will be identified with a numerical code. Only those medical history data that are related to the study will be subject to verification. This verification will be carried out in the presence of the Principal Investigator/Collaborating Investigators, who are responsible for guaranteeing the confidentiality of all the data in the medical records belonging to the subjects participating in the study. The data collected for the study will be identified by a code and only the Principal Investigator/Collaborators will be able to relate these data to the patient and his/her clinical history.

Therefore, the participant’s identity will not be disclosed to any other person except to health authorities, when required or in cases of medical emergency. The Research Ethics Committees will only have access to verify the personal data, the clinical study procedures and the compliance with the norms of good clinical practice (always maintaining the confidentiality of the information).

The Investigator and the Sponsor will keep the data collected for the study for at least 10 years after its completion.

The Data Protection Officer of the study (person in charge of data processing and to whom the patient can address to exercise the rights of access, modification, opposition, cancellation of data, limit the processing of data that are incorrect, request a copy or transfer to a third party (portability) of the data collected for the study) is available at this address: [contact].

### Plans for collection, laboratory evaluation and storage of biological specimens for genetic or molecular analysis in this trial/future use {33}

Not applicable. Biological specimens for genetic or molecular analysis will not be collected.

